# Design of COSMIC: a randomized, multi-centre controlled trial comparing conservative or early surgical management of incomplete cervical cord syndrome without spinal instability

**DOI:** 10.1186/1471-2474-14-52

**Published:** 2013-01-31

## Abstract

**Background:**

Incomplete cervical cord syndrome without spinal instability is a very devastating event for the patient and the family. It is estimated that up to 25% of all traumatic spinal cord lesions belong to this category. The treatment for this type of spinal cord lesion is still subject of discussion. From a biological point of view early surgery could prevent secondary damage due to ongoing compression of the already damaged spinal cord. Historically, however, conservative treatment was propagated with good clinical results. Proponents for early surgery as well those favoring conservative treatment are still in debate. The proposed trial will contribute to the discussion and hopefully also to a decrease in the variability of clinical practice.

**Methods/Design:**

A randomized controlled trial is designed to compare the clinical outcome of early surgical strategy versus a conservative approach. The primary outcome is clinical outcome according to mJOA. This also measured by ASIA score, DASH score and SCIM III score. Other endpoints are duration of the stay at a high care department (medium care, intensive care), duration of the stay at the hospital, complication rate, mortality rate, sort of rehabilitation, and quality of life. A sample size of 36 patients per group was calculated to reach a power of 95%. The data will be analyzed as intention-to-treat at regular intervals, but the end evaluation will take place at two years post-injury.

**Discussion:**

At the end of the study, clinical outcomes between treatments attitudes can be compared. Efficacy, but also efficiency can be determined. A goal of the study is to determine which treatment will result in the best quality of life for the patients. This study will certainly contribute to more uniformity of treatment offered to patients with a special sort of spinal cord injury.

**Trial Registration:**

Gov: NCT01367405

## Background

Traumatic Central Cord Syndrome (TCCS) was considered as a separate clinical entity. The most characteristic feature is disproportionately more motor impairment of the arms (especially the hands) than the legs, bladder dysfunction and varying degrees of sensory loss below the lesion.

Recently, it has been shown that the distinction of TCCS with an incomplete cervical spinal cord lesion (ICSCL) is artificial [1]. It is the most frequent incomplete traumatic spinal cord lesion. It accounts for up to 70% of all incomplete cervical spinal cord lesions [2], although the exact incidence is not known.

Uncertainty exists about the treatment. A good recovery has been described after conservative treatment [3]. Conservative therapy was usually considered when a fracture or dislocation of the spine was absent. It is often seen in hyperextension trauma in the elderly, with a degenerative spondylotic stenotic cervical spine. However, some reports suggest a better outcome after surgical decompression [4]. Randomized trials have not been performed.

Since the economic and emotional impact of a spinal cord lesion is enormous, optimal treatment should be instituted immediately after the traumatic event. To provide more evidence in the choice of a treatment for a specific traumatic spinal cord lesion, this study has been designed.

## Methods/Design

### Ethical approval

The study has been approved by the regional ethical board CMO Arnhem – Nijmegen.

### Goal of the study

This study will evaluate two strategies to improve functional outcome in patients with ICSCL without a fracture or instability of the cervical spine: 1) early decompressive surgery, and 2) conservative treatment.

### Eponym

COSMIC is an eponym for Conservative or Surgical treatment for Incomplete Cord lesion.

### Definition ICSCL without spinal instability

ICSCL is an incomplete spinal cord lesion due to a cervical spine trauma. Spinal instability is considered when the criteria defined by White and Panjabi are present [5]. At MRI and CT scanning with multiplanar reconstruction signs are not seen that could indicate a fracture of the cervical spine or instability. An overt sequestrated herniated disc should not be present since this will always necessitate immediate surgery. Involvement of the cervical spinal cord should be established at physical examination (symptomatic arm or hand dysfunction is obligatory).

### Surgical strategy

Several predictive factors for a good outcome have been identified. One is the timing of surgery after the injury. The debate about early versus late decompression is still not closed. Early has been defined rather broadly from less than 24 hours to less than 14 days [3,4,6].

From a biological point of view, it seems logical to decompress a neural structure as soon as possible to provide an optimal chance for recovery of the function. Since most patients will not be directly referred to the hospital where the surgical treatment will be offered, time for transfer of the patient should be included. Therefore in this study, early decompression is defined as within 24 hours after the injury. A recent meta-analysis on timing of decompressive procedures in cases of traumatic spinal cord injuries accompanying spinal fractures or dislocations, also considered a surgical decompression within 24 hours post-injury as early [7]. In this trial, patients allocated to the surgical strategy will be offered surgery within 24 hours post-injury. The main goal of the surgery is adequate decompression of the spinal cord.

### Hypotheses

H_0_: In patients with ICSCL without spinal instability, functional outcome for both strategies is the same.

H_1_: In patients with ICSCL without spinal instability, the early surgical strategy improves functional outcome compared to conservative treatment.

### Patient selection

To avoid discussion about possible confounding or effect modification related to the mechanism of trauma, this study will focus on ICSCL in patients without fracture or instability of the cervical spine on radiological examinations. Instability is established with MRI, CT, lateral and anteroposterior plain radiographs of the spine. In case of doubt, radiographs in sitting position or dynamic radiographs are made under direct supervision of the treating surgeon.

Inclusion criteria: all adult patients with a history of a traumatic event to the cervical spine fulfilling the criteria of ICSCL.

Exclusion criteria: cognitive impairments, known neurological disease, psychiatric illness, significant co-morbidity interfering with the indication to perform surgery or not, use of anti-coagulating drugs, addiction to drugs or alcohol (more than five units daily), not speaking Dutch language fluently, not willing to participate or participating in another trial.

### Treatment allocation

After written informed consent has been obtained patients will be randomized to either surgical or conservative treatment. Informed consent should be obtained within two hours after arrival at the emergency department. Although no mode of treatment has been proven superior to the other, surgical decompression may be warranted during the conservative strategy treatment. It is not considered as a failure but as a part of the conservative strategy.

### Interventions

Surgical treatment will consist of decompression of the spinal cord by an anterior, posterior or combined approach. The choice for the approach is made by the treating surgeon. All participating surgeons are experienced in spinal surgery. Fixation may be added to the decompressive surgery according to the preference of the treating surgeon. Procedure and use of implants will be documented. If a patient is allocated to the surgery group it should be executed within 24 hours post-injury. Postoperatively, an intensive rehabilitation program will be prescribed. This will include exactly the same elements as for those patients who were allocated to the conservative treatment.

Conservative treatment will consist of an intensive rehabilitation program including physiotherapy and ergotherapy. However, when a patient deteriorates after 24 hours post-injury, surgery may be indicated. This decision is made by the treating physician. Should a patient be operated upon after he has been located to the conservative group, it is not considered as a failure of the conservative strategy, but as a possible consequence in case of deterioration.

### Outcomes

Primary outcome: functional outcome at two years as measured by validated Dutch translation of mJOA.

Secondary outcomes: motor and sensory scores according to the ASIA standards at six weeks, 12 weeks, 12 months, duration of the stay at a high care department (medium care, intensive care), duration of the stay at the hospital, complication rate, mortality rate, sort of rehabilitation, quality of life, SCIM III, and arm/hand function assessed by the disability of the arm, shoulder and hand questionnaire (DASH).

Furthermore, subjects keep a diary on the financial consequences and health care consumption related to ICSCL. Visits to the general practitioner, physical therapist, medical specialists, alternative health practice, use of analgesics, duration of sick leave from work and additional utility/mobility costs are recorded. The patient’s or diaries are returned during the outpatient clinic visits or by mail.

### Scales

#### mJOA

The scale was developed for evaluation of impairments related to degenerative spondylotic changes in the cervical spine. Nevertheless, this scale is very useful since it suitably describes the functional limitations of a patient with compromised function of the cervical spinal cord. The translation into the Dutch language has been validated [8]. The minimal clinical important difference has been estimated [9]. Since the patient can complete the questionnaire himself, the scale is functional and a minimal clinical important difference has been estimated, the mJOA is used as a primary outcome measurement.

#### SCIM III

The Spinal Cord Independence Measure (SCIM III) is also a functional score that has been developed to evaluate the functional recovery of patients with a spinal cord lesion. It can be easily completed even by phone. Recently, its reliability and validity has been shown [10] however, a minimal clinical important difference has not been established.

#### ASIA

The score of the American Spinal Injury association (ASIA score) is the most frequently used scale to grade neurological level and the severity of spinal cord injury. The ASIA motor score represents the muscle strength of determined muscles in arms and legs and the ASIA sensory score represents the light touch and pin-prick sensory functions within all dermatomes. The score is reduced to upper extremity motor score (range 0–50), lower extremity motor score (range 0–50) and sensory score (range 0–112).

#### EuroQol 5QD (EQ-5D)

EQ-5D is a standardized health-related quality of life questionnaire that can be applied to a wide range of health conditions and treatments. It is designed for self-completion by respondents. It consists of a descriptive part compromising five dimensions: mobility, self-care, usual activities, pain/discomfort and anxiety/depression, and a VAS score indicating the self- rated health on a 20 cm VAS scale.

#### DASH

The DASH was developed as a 30-item questionnaire to be completed by the patient to assess functional status for clinical use in daily practice or as a research tool. DASH evaluates symptoms and physical function with a five-response option for each item. It has been proven to be a reliable and valid instrument to assess disability in patients with a variety of upper limb disorders [11]. The Dutch translation has been validated [12].

### Evaluation patients

The nature of the treatment under in the study prevents a completely blind evaluation of the outcome. Therefore, an independent observer trained in neurological examinations, will perform the physical examination at each follow- up visit. He/she will also complete the questionnaires and check the self-assessed questionnaires on completeness (Table 1). The independent observer will not participate in the initial admission, randomization and treatment of the patient.

**Table 1 T1:** Study measurements over time

	**Admission**	**6 weeks post**-**injury**	**12 weeks post**-**injury**	**12 months post**-**injury**	**24 months post**-**injury**
Patient demographics	X				
ASIA	X	X		X	X
mJOA	X	X	X	X	X
SCIM III	X	X	X	X	X
DASH	X	X		X	X
EQ-5D	X	X	X	X	X
Patient diary	X	X	X	X	X
Complication registration		X	X	X	X
MRI	X				
CT with reconstruction	X				

### Data collection

Data will be collected during/each patient contact through an internet based database. Investigators have access to data, but do not have the possibility to check the results during the trial. Neither do they have any possibility to correct data. If required, data can be changed by an independent supervisor of the database.

### Design

The study has been designed as a multi-centre, open, randomized controlled trial. Participating centres should have adequate experience with the treatment of patients with spinal cord trauma and neurosurgical facilities should be available on a 24 hours-a-day basis. All primary analyses will be performed on an intention-to-treat basis comparing the two strategies.

### Randomization

To improve the balance in the number of treatment assignments in each participating centre, randomization will be performed in blocks. A computer generated list of treatment allocation is used for randomization. Treatment assignment is made by secure computer access.

### Sample size

Power calculations are hampered by the scarcity of data on clinical outcome in this patient group. The minimal clinically important difference in mJOA has been estimated in an earlier trial [9,13]. A difference of at least two points on the modified JOA functional score is considered significant. The difference is expected to be mainly allocated to the function of the arms and legs. Based on literature, a standard deviation of 2 is assumed. This estimate was confirmed by asking three experienced cervical spine surgeons (members of the board of the CSRS-es).

The sample size is calculated as follows: a two group student test with a 0.05 two sided significance level and a power of 95 % will need a sample size per group of 27 to detect a significant difference. Considering a ten percent loss in follow up a total of 30 individuals per group need to be included.

During the conservative treatment some patients will require surgical decompression due to for example neurological deterioration. It is estimated that it will occur in 20% of the patients. Although this is not considered a failure of treatment, the sample is increased to 36 patients per group in order to maintain the same power.

Only patients allocated to the conservative group who are offered surgery within 24 hours post-trauma, are considered crossovers. This number is expected to be very low. However, after completion of the trial this will be evaluated and a separate per-protocol analysis performed if significant cross over occurred.

Five centres in the Netherlands will participate and is estimated that its conclusion will be within 2 years.

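### Crossover is defined in the conservative arm only and by an offer of surgery, so missed early surgery in the surgical arm can neither count as crossover nor trigger the per-protocol analysis

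*Protocol article*

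**What the plan says.** The crossover rule is in the protocol article, Sample size: "Only patients allocated to the conservative group who are offered surgery within 24 hours post-trauma, are considered crossovers". The article adds of these patients: "This number is expected to be very low". After the trial is complete their number is to be evaluated, with "a separate per-protocol analysis performed if significant cross over occurred". No figure is attached to the word significant.

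For the surgical arm, Interventions says: "If a patient is allocated to the surgery group it should be executed within 24 hours post-injury". Surgical strategy puts it as an offer: "patients allocated to the surgical strategy will be offered surgery within 24 hours post-injury". No section classifies a surgical-arm patient who is operated on later than that, or not at all.

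For the conservative arm, Treatment allocation says of decompression during that strategy: "It is not considered as a failure but as a part of the conservative strategy". Interventions ties such surgery to deterioration after the first 24 hours and says "it is not considered as a failure of the conservative strategy, but as a possible consequence in case of deterioration".

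The main analysis set is given under Design: "All primary analyses will be performed on an intention-to-treat basis comparing the two strategies".

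**The concern.** A per-protocol analysis is useful only if departures from allocated treatment are recognised in both arms and judged by what patients received. This rule does neither. Its opening word confines crossover to one arm, although surgery within 24 hours is what distinguishes the surgical arm. It also turns on an offer, so a patient who stayed on the allocated treatment can be labelled a departure.

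The trigger inherits the asymmetry. Non-adherence in the surgical arm, however common, is not crossover and cannot prompt the analysis. With no threshold, the decision whether to run it is left to judgement after the trial ends. At stake is whether the secondary, adherence-based result can be interpreted. The primary comparison is not at stake.

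**Working it through.** **1. The plan's own figures.** Inputs from Sample size: difference 2 mJOA points, SD 2, two-sided alpha 0.05, power 95%. A two-sample t-test (noncentral t) needs 26.99, so 27 per group, with power 0.9501 at 27. Allowing for 10% loss, 27/0.9 = 30. The 20% allowance gives 30 × 1.2 = 36 (dividing instead, 30/0.8 = 37.5, so 38). The stated 27, 30 and 36 reproduce. The point here does not depend on them; they supply the 2-point difference, the SD and the arm size.

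**2. Applying the rule case by case.**

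| Allocated to | Surgery | Received what the arm calls for? | Crossover under the rule? |
|---|---|---|---|
| Surgery | Within 24 hours | Yes | No |
| Surgery | After 24 hours, or never | No, by Interventions | No |
| Conservative | Received within 24 hours | No | Yes |
| Conservative | Offered within 24 hours, declined | Yes | Yes, read literally |
| Conservative | After 24 hours, on deterioration | Yes, part of the strategy | No |

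The second and fourth rows are misclassified. A surgical-arm patient who declines a timely offer also fits the wording in Surgical strategy (offer) but not that in Interventions (execution).

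**3. The trigger.** Suppose, as an assumption, that 30% of the surgical arm misses early surgery (0.30 × 36 = 10.8, about 11 patients) and no conservative patient is offered it. The crossover count is 0, so the condition for the analysis is not met.

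**4. Size if such patients are retained.** Assumptions, none of them from the documents: a fraction q of the surgical arm misses early surgery; these patients have the conservative-arm mean; the true difference is 2 points. The expected difference is then (1 − q) × 2 + q × 0 = 2(1 − q). Power is for a t-test with SD 2 and 32 evaluable per arm (36 × 0.9 = 32.4).

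| q (assumed) | Expected difference | Power |
|---|---|---|
| 0 | 2.0 | 0.976 |
| 5% | 1.9 | 0.96 |
| 10% | 1.8 | 0.94 |
| 20% | 1.6 | 0.88 |
| 30% | 1.4 | 0.79 |

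**5. Removing conservative crossovers.** Let a fraction c of the conservative arm be removed, with a mean s points away from the remaining patients. The full-arm mean is the remaining mean plus c × s, so removal shifts the arm mean by −c × s. With s = −2 (early deteriorators, assumed), the conservative mean rises by 0.1 at c = 5% and 0.2 at c = 10%. That narrows the difference further, so it adds to the dilution in step 4. With s = +2 the sign reverses.

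**The case against.** The strongest reply is that the article defines crossovers but never says who belongs to the per-protocol set. A patient who is not a crossover is not thereby per-protocol. Interventions says surgery in that arm should take place within 24 hours, so the full protocol or analysis plan, which is not shown, could exclude late or unoperated patients. This stands. A reader might infer that the planned analysis keeps these patients and is biased; the documents support that only for a set built on the stated rule alone.

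The rule follows a paragraph on surgery during conservative treatment, so its opening word may be meant mainly to separate surgery in the first 24 hours from later surgery. That is plausible, but the sentence still restricts crossover to one arm, and nothing else covers the surgical arm. Likewise, offered may loosely mean given, as it may in Surgical strategy. Then the patient who declines is an edge case, and plainer wording removes it.

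Four other readings are tempting but not supported:

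- **Treatment allocation and Interventions contradict the crossover rule.** Interventions uses the same 24-hour boundary, and Treatment allocation states the allowance in general terms.
- **Referral from other hospitals makes late surgery likely.** The article gives transfer time as the reason for the length of the window, and reports no rate of late surgery.
- **The decision to run the analysis follows sight of the outcomes.** The text says only that the number of crossovers is evaluated after completion.
- **Removing early deteriorators offsets the dilution.** Step 5 shows that it adds to it.

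**Conclusion.** The point holds as a defect in a stated rule. Crossover is one-sided and offer-based, and the per-protocol analysis depends on a trigger with no threshold that surgical-arm non-adherence cannot reach. This follows from the wording, however the per-protocol set is later defined.

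The numerical consequence is conditional. A true 2-point difference would appear as 1.8 at q = 10% and 1.6 at q = 20% (1.9 to 1.4 over 5% to 30%) if patients who miss early surgery are retained and have the conservative-arm mean. If missing surgery is related to prognosis, the direction could differ. The actual size cannot be computed from the documents.

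The weight is moderate: the analysis is secondary and conditional, and the primary intention-to-treat result is unaffected. The change is still worth making, because the present rule is wrong as stated and cheap to correct.

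**What to change.** Replace the crossover sentence in Sample size with a definition of non-adherence that covers both arms, based on surgery actually received and its time from injury, using the protocol's existing 24-hour limit:

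- allocated to surgery and not operated on within 24 hours;
- allocated to conservative treatment and operated on within 24 hours.

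Later surgery in the conservative arm stays part of that strategy, as the article already says. State that the adherence analysis is always run, label it a sensitivity analysis to the intention-to-treat result, and delete the condition that significant crossover has occurred. State who is in the per-protocol set in the same place. A complier average causal effect, with randomisation as the instrument, would avoid simple exclusion of selected patients, but it is optional.

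The cost is a change of wording, recording the time of injury and of surgery for every patient operated on, and one extra sensitivity analysis. The sample size does not change.

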### Statistical analysis

Baseline characteristics are reported using descriptive statistics. Any imbalance characteristics found visually will be account for in analysis of primary outcome.

Since the primary outcome of the two strategies is compared after two years, a test for independent samples will be used (student-t test). To see if differences at all time points are present, these are assessed by computing both the main effect of the treatment and the interaction between treatment and time in a mixed linear model.

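### The primary model for two-year mJOA depends on which baseline imbalances look notable, so the nominal 5% level is not assured; one model with admission mJOA and centre should be fixed in advance

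*Protocol article*

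**What the plan says.** The primary outcome (Outcomes) is "functional outcome at two years as measured by validated Dutch translation of mJOA". For its comparison between arms, Statistical analysis says that "a test for independent samples will be used (student-t test"), in line with the Sample size section, which is built on "a two group student test with a 0.05 two sided significance level and a power of 95" percent.

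The paragraph before the test is named, in the same section, says: "Any imbalance characteristics found visually will be account for in analysis of primary outcome". It does not say which characteristics are inspected, how large a difference counts, what model is then fitted, when the inspection takes place, or whether the adjusted or the unadjusted result is primary.

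Two pieces of baseline information are known in advance. Table 1 ("Study measurements over time") schedules mJOA at admission. The Randomization section says: "To improve the balance in the number of treatment assignments in each participating centre, randomization will be performed in blocks". Neither admission mJOA nor centre is named in the primary analysis. The mixed linear model in Statistical analysis is meant for differences across all time points and names no covariates. The Design section describes a "multi-centre, open, randomized controlled trial".

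**The concern.** After proper randomisation, any baseline imbalance has arisen by chance. Choosing covariates by visible imbalance therefore selects on chance, not on how well a characteristic predicts outcome. A t-test cannot carry covariates, so the two statements describe at least two possible primary analyses and no rule for choosing between them.

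At stake is the meaning of the primary p-value. If the model is settled by inspecting the data, the error rate need not be 5%, and its direction depends on how the inspection is done. A secondary matter is efficiency: if admission mJOA or centre predicts outcome, leaving it out makes the standard error larger than it need be.

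This is not a detail left to a statistical analysis plan. The article states the covariate rule, and a later plan would have to replace it, not merely elaborate it.

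**Working it through.** **Inputs from the protocol article.** Difference 2 points, SD 2, two-sided 0.05, power 95%, 27 then 30 then 36 per arm, 10% loss (Sample size); five centres ("Five centres in the Netherlands will participate"); mJOA at admission (Table 1).

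**Assumptions, not in the document.** Correlation r between admission and two-year mJOA of 0.3, 0.5 or 0.7; a cut-off of 0.25 SD for a visible imbalance; normal outcomes.

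**1. The plan's own figure.** The exact noncentral-t calculation for a standardised difference of 2/2 = 1 gives 26.99, so 27 per arm. Then 27/0.9 = 30 and 30 × 1.2 = 36. The stated sizes reproduce. Completers: 36 × 0.9 = 32.4, taken as 32 per arm.

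**2. How often the rule would be triggered.** For one characteristic with 36 per arm, P(|standardised difference| > 0.25) = 2[1 − Φ(0.25/√(2/36))] = 2[1 − Φ(1.06)] = 0.289. With 32 per arm it is 2[1 − Φ(0.25/√(2/32))] = 2[1 − Φ(1)] = 0.317. For at least one of five independent characteristics it is 1 − (1 − 0.317)^5 = 0.85. At cut-offs of 0.4 and 0.5 SD the last figure is 44% and 21%.

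**3. Type I error.** Simulated trials with no treatment effect, 32 per arm, one covariate:

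| Procedure | r = 0.3 | r = 0.5 | r = 0.7 |
|---|---|---|---|
| Adjust only if difference > 0.25 SD | 4.2% | 3.7% | 2.4% |
| Take the smaller of the t-test and adjusted p-values | 6.0% | 7.2% | 7.8% |
| Pre-specified ANCOVA | about 5% | about 5% | about 5% |

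Repeat runs moved the first two rows by up to about half a point (for example 4.6% in the first cell) and left the pattern unchanged. With five covariates and cut-offs of 0.25 to 0.5 SD, the mechanical rule gave 1.9% to 3.7%, and taking the smallest p-value gave 9.1% to 10.4%.

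**4. Power.** Unadjusted standard error = 2√(2/32) = 0.50. With ANCOVA the SD becomes 2√(1 − r²) = 1.908, 1.732 or 1.428, and the standard error 0.48, 0.43 or 0.36. Noncentral-t power with 32 per arm, ignoring the few degrees of freedom used by covariates:

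| True difference | t-test | r = 0.3 | r = 0.5 | r = 0.7 |
|---|---|---|---|---|
| 2.0 (protocol) | 97.6% | 98.5% | 99.5% | >99.9% |
| 1.6 (assumed) | 88.3% | 91.0% | 95.3% | 99.3% |

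The 1.6 is 2 × (1 − 0.20). It supposes that the 20% of conservative-arm patients expected to have later surgery gain the full benefit. The protocol does not say this.

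**5. Centre.** Simulation with five centres, 6 per arm in each, and a t-test that ignores centre gave type I error of 4.6%, 4.2% and 3.3% at assumed intraclass correlations of 0.05, 0.10 and 0.20. At 0.20 and 1.6 points, power was 89.4% unadjusted against 92.5% adjusted for centre.

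**The case against.** The strongest reply is that the plan works on its own figures. The t-test is a legitimate primary analysis, it matches the test used for sample size, and it exceeds the 95% power target at 2 points. The two statements can be read together as a t-test by default with an adjusted version when imbalance is seen. Applied mechanically, such a rule is conservative and is no less powerful than the t-test: at r = 0.5 and 1.6 points it has about 92% power, against 88% for the t-test and 95% for ANCOVA. Covariate lists are often left to an analysis plan.

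Most of this stands and limits the point. It does not rescue the sentence, because even the conciliatory reading leaves covariates, threshold and timing open.

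Three stronger readings are tempting and should be resisted:

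- **That the sponsor will pick among p-values.** The text says imbalance will be accounted for; it offers no choice of the best result. The 6% to 8% shows what the wording fails to prevent, not what is planned.
- **That covariates will be chosen with outcomes known.** The article does not say when baseline is inspected, and baseline data exist long before two-year outcomes. Data collection bars investigators from checking results during the trial. The abstract mentions analysis at regular intervals, so the risk is open, but it is not stated.
- **That admission mJOA is the strongest predictor, or that the trial is underpowered without it.** No baseline-outcome correlation is given, ASIA and SCIM III are also recorded at admission, and the larger power gains need the assumed 1.6-point difference.

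**Conclusion.** The point holds in limited form: the article fixes a data-dependent covariate rule for the primary outcome, so the primary model is not determined in advance and the nominal 5% is not assured. The direction of the departure depends on use. It is conservative (about 2.4% to 4.2%) under a mechanical 0.25 SD cut-off and inflated (about 6% to 8%) if the discretion is used to favour the smaller p-value. Both ranges are for one covariate, 32 per arm and assumed correlations of 0.3 to 0.7, give or take half a point of simulation error.

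The t-test by itself is valid, and slightly conservative if centres differ. Efficiency is a minor gain at the protocol's 2-point difference (1 to 2.4 percentage points of power). It becomes material only if the effect is diluted, and then only if admission mJOA or centre is prognostic. This should be fixed before analysis, but it is not a fatal flaw.

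**What to change.** Replace the visual-imbalance sentence with one pre-specified primary analysis: a linear model of 24-month mJOA on treatment, with admission mJOA and centre as fixed covariates, on the intention-to-treat population. Keep the unadjusted t-test as a supporting analysis. Label adjustment for any other baseline characteristic as sensitivity or exploratory, whatever imbalance is seen.

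The cost is analysis wording and about five degrees of freedom: one for admission mJOA and 5 − 1 = 4 for centre, which takes the residual from 64 − 2 = 62 to 57 with 32 completers per arm. No extra patients or measurements are needed, and the planned 36 per arm still suffices.
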